# Prospective, Multicenter, Observational Study to Evaluate a Cell-Impermeable Endoprosthesis for Treatment of Stenosis or Occlusion within the Dialysis Outflow Circuit of an Arteriovenous (AV) Fistula or AV Graft (The WRAP Registry)

**DOI:** 10.1007/s00270-023-03531-w

**Published:** 2023-08-17

**Keywords:** Hemodialysis, Patency, Occlusion, Stenosis, WRAPSODY Cell-Impermeable Endoprosthesis

## Abstract

**Purpose:**

Dysfunctional vascular access due to stenosis/occlusion within the arteriovenous fistula or graft (AVF/AVG) negatively affects the clinical management of patients undergoing hemodialysis. Results from the feasibility study of the WRAPSODY™ Cell-Impermeable Endoprosthesis demonstrated that the device can achieve high patency rates and maintain integrity of the dialysis outflow circuit. This study was designed to assess real-world evidence of safety and efficacy outcomes following device placement.

**Materials and Methods:**

This is a prospective, multicenter, non-investigational, post-market observational study of 500 patients at up to 50 centers worldwide with a mature AVF/AVG dialysis access (≥ 1 hemodialysis session) who experience stenosis/occlusion of the outflow circuit prior to placement of WRAPSODY. Patients will be divided into the following two cohorts: peripheral or central thoracic. Primary outcome measures include target lesion primary patency (TLPP) at 6 months and procedure and/or device-related events through 30 days post-procedure. Secondary outcome measures include TLPP, safety events, and the number of interventions needed to maintain patency through the 24 month study period. Exploratory endpoints include time to access abandonment, resumption of successful dialysis, functional patency, and pending available imaging data, any incidence of stent fractures, migration, or edge stenosis. Study enrollment began in June 2022, the last patient visit is expected in 2026.

**Discussion:**

It is expected that this study will provide real-world evidence regarding the performance of the WRAPSODY device in a diverse population of patients, which may encourage its use in the continuum of hemodialysis access management.

**Trial Registration:**

NCT05062291

**Graphical Abstract:**

[figure not shown]

## Introduction

Hemodialysis is the most common form of kidney replacement therapy, accounting for nearly 90% of all dialysis methods [1, 2]. The success of hemodialysis requires continuous function of a vascular access that is traditionally accomplished through the creation of an arteriovenous fistula (AVF) or implanting an arteriovenous graft (AVG) [3, 4]. However, complications such as stenosis and/or occlusion are a leading cause of failure in the AVF and AVG, which can interfere with the ability of patients to undergo hemodialysis, resulting in potentially increased morbidity and life-threatening consequences [4–6].

Treatment options to adequately manage dysfunctional vascular access due to stenosis/occlusion are associated with limited patency. Surgery may assist with achieving extended patency of the access circuit, however, high rates of morbidity due to trauma preclude it from becoming a commonly employed treatment strategy and is instead reserved for non-salvageable vascular accesses [7–9]. A common endovascular alternative for the clinical management of venous stenosis/occlusion includes use of percutaneous transluminal angioplasty (PTA) [7, 10–14]. However, patency of PTA can vary widely, with average reported cumulative primary patency rates of 61% and 47% at 6 and 12 months, respectively [15], which often requires re-intervention(s) to maintain patency. Within the past 30 years, covered stents have emerged as an alternative to PTA to maintain patency of the hemodialysis access circuit [16]. The proposed advantages of covered stents over PTA are their stable and relatively inert matrix to support endothelialization coupled with their structural rigidity to help maintain patency of the circuit [17]. However, even with early covered stents, patency rates have been reported to decline over time with one study reporting approximately 70% of patients requiring re-intervention within one year of placement [18]. As a result, there has been an impetus to continue to innovate covered stents to improve patency of vascular access for hemodialysis.

The WRAPSODY™ Cell-Impermeable Endoprosthesis, a novel covered stent, was developed to help improve long-term vascular access. The device is a self-expanding endoprosthesis composed of a single nitinol wire encased between layers of fluoropolymer that helps to reduce stenosis and thrombus formation. A preclinical study that examined rates of stenosis following placement of the WRAPSODY device versus a conventional covered stent found that the device was associated with significantly lower rates of stenosis (2.1% vs. 10.3%, *p* = 0.009) [19]. Findings from the first-in-man study of the WRAPSODY device, that included 46 patients with access circuit stenosis treated with the device, demonstrated primary patency rates of 97.7% and 84.6% at 6 and 12 months, respectively, [20]. Based on the results of the first-in-man study in 2020, the WRAPSODY device received CE Mark approval.

Despite the promising efficacy outcomes associated with the WRAPSODY device [19, 20], there is an unmet need for real-world data describing clinical outcomes associated with the device, particularly in a large patient population. To help address this need, we describe the design of a prospective, multicenter, post-market, observational study (the WRAP Registry) that will document real-world data for safety and efficacy outcomes following use of the WRAPSODY device in 500 patients.

## Methods

### Study Design

The WRAP Registry is a prospective, multicenter, non-investigational, non-randomized, post-market, observational study conducted at up to 50 centers throughout Australia, Europe, New Zealand, and South America.

### Compliance with Ethical Standards

This study complies with the 1964 Helsinki Declaration and its later amendments. Ethics approval has been granted by the local ethics committees for each center participating in the study.

### Inclusion and Exclusion Criteria

The full inclusion and exclusion criteria are provided in Table 1. As this study seeks to describe the safety and efficacy outcomes associated with the use of the WRAPSODY device in a real-world population, the eligibility criteria are intentionally minimal to help capture the full range of clinical profiles of the study population and avoid bias for, or against, specific subgroups (e.g., disease states, anatomies).

**Table 1 Tab1:** Full inclusion and exclusion criteria

Inclusion criteria	Exclusion criteria
Patient provides written informed consent for study participation	Patient has a planned surgical revision of access site
Patient is male or female, with an age ≥ 18 years at date of enrollment	Patient has a known or suspected infection of the hemodialysis access site, systemic infection, and/or septicemia
Patient is willing to comply with site standard of care procedures and follow-up visit schedules over 24 months	Patient has an uncorrectable coagulation disorder
Patient is undergoing chronic hemodialysis using the hemodialysis access that the intervention will be performed upon	Known hypersensitivity to nickel titanium alloy
The dialysis access is considered mature and has been used to deliver hemodialysis treatments for at least one session	Patient's hemodialysis access is anticipated to be abandoned within 6 months
Patient has stenosis or occlusion within the dialysis outflow circuit of an AV fistula or AV graft and is treated with the WRAPSODY Cell-Impermeable Endoprosthesis System in accordance with device Instructions for Use	Patient is scheduled for kidney transplant or peritoneal dialysis within the next 6 months post-procedure
	Full expansion of a PTA balloon cannot be achieved during predilatation
	Device would be placed in the superior vena cava
	Any inflow or outflow lesion that could jeopardize patency access long-term beyond the target treatment area

AV, arteriovenous; PTA, percutaneous transluminal angioplasty

### Study Cohort

Up to 500 adults, across participating centers, with stenosis or occlusion within the dialysis outflow circuit who meet the inclusion and exclusion criteria (Table 1) will be classified into one of two cohorts based on location of stenosis/occlusion: peripheral cases in both AVG and AVF or thoracic central cases in both AVG and AVF. Thoracic central cases will include the subclavian vein, brachiocephalic/innominate vein, and superior vena cava. Peripheral cases will include veins distal to the axillary vein at the junction of the entry of the cephalic vein (cephalic arch).

### Study Procedures

#### Screening and Enrollment

All consecutive patients who meet the eligibility criteria will be considered for enrollment in the study and provided additional information on the study, including informed consent.

All patients who are treated with the WRAPSODY device will be considered enrolled in the study. If the device is inserted into vasculature and treatment is attempted but the procedure is terminated without delivery of the covered stent, the only data collected will be device failure, malfunction details, and/or device-related adverse events. These patients will be followed through discharge for safety events only and exited from the study.

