### Primary Outcome Measures

The primary outcome measures focus on the efficacy and safety of the device and generally align with standardized definitions reported previously [21, 22].

The primary efficacy outcome measure is the proportion of patients with target lesion primary patency (TLPP) at 6 months. TLPP is defined as freedom from clinically driven target lesion revascularization or target lesion thrombosis measured through 6 months post-procedure, which is the time interval of uninterrupted patency following the study procedure to the next intervention performed on the target lesion, or uncorrectable target lesion occlusion.

The primary safety outcome measure is the proportion of patients without any localized or systemic safety events through 30 days post-procedure that affect the access or venous outflow circuit and result in reintervention, hospitalization, or death (not including stenosis or thrombosis).

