### Additional Outcome Measures Assessed

Secondary outcomes will include the proportion of patients with: TLPP at 12 and 24 months; assisted TLPP at 6, 12, and 24 months (defined as the time to loss of assisted primary patency of the target lesion, which is the time from the study procedure to uncorrectable target occlusion); access circuit primary patency at 6, 12, and 24 months (defined as time to loss of primary patency); post-procedure secondary patency outcomes at 6, 12, and 24 months (defined as the interval post-procedure until access circuit abandonment). Additional secondary outcome measures include serious adverse events across the 24 month study period, number of device observations, number of interventions to maintain access circuit patency, number of target lesion re-interventions to maintain target lesion patency, as well as the percentage of patients with device success, procedural success, and anatomic success.

Pending data availability, additional outcome measures will include index of patency function at 6, 12, and 24 months (defined as the time from the initial study procedure to complete access abandonment divided by the number of venous outflow circuit re-interventions to maintain hemodialysis); clinical success (defined as resumption of successful dialysis through existing access for ≥ 1 session post-procedure); functional patency of the access (defined as the ability to support dialysis) at 6, 12, and 24 months. Provided follow-up imaging is collected as part of the standard of care, additional outcome measures will include the incidences of reported stent fractures, migration, and edge stenosis.

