### Statistics

Data will be organized into two analytical sets: an intent-to-treat (ITT) analysis set and a per-protocol (PP) analysis set. The ITT analysis set will include all patients enrolled in the study and will be considered the primary analysis set for all safety and efficacy outcome measures. The PP analysis set will include all enrolled patients who meet all inclusion and exclusion criteria with no major protocol deviations.

All analyses will be descriptive; no hypothesis testing is planned. Continuous variables will be summarized using mean, standard deviation, median, minimum, and maximum. Categorical variables will be summarized using frequencies and percentages will be reported with their associated confidence intervals. Time-to-event data will be summarized using Kaplan–Meier curves. All data will be analyzed using SAS version 9.4, or later (SAS Institute Inc., Cary, NC).

The sample size of 500 was determined to be sufficient to accurately characterize use of WRAPSODY in real-world practice based on clinical consensus of the study’s principal investigators. An interim analysis is not currently planned.

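### Patients in whom the stent is inserted but not delivered have no planned data from discharge to day 30, so the 30-day primary safety outcome cannot cover every attempt

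*Protocol article*

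**What the plan says.** Four places in the protocol article bear on this.

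- **Screening and Enrollment, who is enrolled:** "All patients who are treated with the WRAPSODY device will be considered enrolled in the study". Table 1 likewise makes treatment with the device, following its instructions for use, an inclusion criterion.
- **Screening and Enrollment, procedures ended without delivery of the stent:** "the only data collected will be device failure, malfunction details, and/or device-related adverse events". The next sentence adds: "These patients will be followed through discharge for safety events only and exited from the study".
- **Statistics:** "The ITT analysis set will include all patients enrolled in the study and will be considered the primary analysis set". This applies to every safety and efficacy outcome.
- **Primary Outcome Measures:** the safety outcome is the "proportion of patients without any localized or systemic safety events through 30 days post-procedure", counting events that affect the access or outflow circuit and lead to reintervention, hospitalization or death, with stenosis and thrombosis left out. The Abstract describes it as covering events related to the procedure, the device or both.

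Additional Outcome Measures Assessed also lists "the percentage of patients with device success, procedural success, and anatomic success", without a definition or a denominator.

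**The concern.** The primary safety outcome has a 30-day window, but one group of patients exposed to the device leaves at discharge. That group is defined by the procedure having gone wrong, so its absence is unlikely to be neutral. A vessel injury during a failed attempt that leads to readmission in the second week is an event the outcome is meant to count, and nothing in the plan would capture it.

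This is a stated data-collection rule and not a detail left to an analysis plan. An analysis plan can say how to handle missing outcomes, but it cannot supply outcomes that were never collected. The registry's purpose is real-world safety evidence, and a reader will take a set labelled ITT to include failed attempts.

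**Working it through.** **Step 1. The two readings of enrolled.** The article does not say whether an undelivered attempt counts as treated.

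| Reading | Support in the text | Consequence for 30-day safety |
|---|---|---|
| Not enrolled | Enrolment and Table 1 require treatment; the undelivered case is described as attempted treatment | Outside the ITT set, which is then an as-treated set selected on delivery |
| Enrolled | The patient is said to exit the study, which implies having been in it | Inside the ITT set, with nothing planned from discharge to day 30 |

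Under both readings the late part of the 30-day window is unobserved for these patients.

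**Step 2. Which events are recorded up to discharge.** One sentence limits the data to device failure, malfunction and device-related adverse events. The next speaks of safety events in general. Table 2, note c, collects both device- and procedure-related events, and all deaths, up to 6 months. For an undelivered attempt it is therefore unclear whether a procedure-related event is recorded, although the outcome counts such events.

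**Step 3. Size.** There is no plan figure to reproduce: the 500 patients rest on clinical consensus, with no rate or precision target. All rates below are assumptions.

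- f = share of attempts that end without delivery: 1%, 2%, 5%
- s = 30-day event-free share in delivered patients: 95%, 98%
- q = 30-day event risk in undelivered attempts: 5%, 20%, 40%, with 100% as the worst case

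If 500 is the number delivered, failed attempts number 500/(1 − f) − 500, or about 5, 10 and 26.

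Event-free share among all attempts = (1 − f)·s + f·(1 − q).

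Overstatement when only delivered patients are counted = s − [(1 − f)·s + f·(1 − q)] = f·(s + q − 1).

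Example: f = 5%, s = 95%, q = 40% gives 0.95 × 0.95 + 0.05 × 0.60 = 93.25%, an overstatement of 1.75 points.

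Overstatement in percentage points:

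| f | s | q = 5% | q = 20% | q = 40% | q = 100% |
|---|---|---|---|---|---|
| 1% | 95% | 0.00 | 0.15 | 0.35 | 0.95 |
| 1% | 98% | 0.03 | 0.18 | 0.38 | 0.98 |
| 2% | 95% | 0.00 | 0.30 | 0.70 | 1.90 |
| 2% | 98% | 0.06 | 0.36 | 0.76 | 1.96 |
| 5% | 95% | 0.00 | 0.75 | 1.75 | 4.75 |
| 5% | 98% | 0.15 | 0.90 | 1.90 | 4.90 |

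The overstatement is zero when q = 1 − s, that is, when failed attempts carry the same risk as delivered ones.

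**Step 4. Comparison with sampling error.** The 95% half-width at n = 500 is 1.96 × √(s(1 − s)/500): 1.9 points at s = 95% and 1.2 points at s = 98%. Of the 18 cells with q up to 40%, only one (f = 5%, s = 98%, q = 40%) exceeds its half-width.

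**Step 5. Success percentages.** If device success meant delivery and the denominator were delivered patients, it would be 100% by construction. Over all attempts it would be 1 − f: 99%, 98% or 95%. The article states neither condition.

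**The case against.** The strongest reply is that this is a descriptive registry with no hypothesis test and no performance threshold, so no formal conclusion turns on a shift of a point or two. Limiting long follow-up to implanted patients is an openly stated choice, and most assumed scenarios fall within sampling error. This stands and limits the severity. It does not remove the gap, because the shift is systematic and the confidence interval does not account for it.

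A reader might also infer three stronger things that the documents do not support.

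- **That device, procedural and anatomic success are computed without the failures.** The article says that device failures and malfunctions are recorded for these patients, so they can be counted. The definitions and denominators may be in the full protocol or analysis plan, which are not shown.
- **That undelivered attempts are scored as event-free.** No passage says so. Under Follow-up, data on patients who withdraw are used up to withdrawal, and missing-data handling is ordinary analysis-plan content. But if these patients were censored at discharge, the analysis would assume that they share the later risk of delivered patients, which is the point in doubt.
- **That procedure-related events are not recorded for them at all.** The reference to safety events, and the index-procedure data listed in Table 2, note b, may cover such events up to discharge. What stands is that adjacent sentences differ in scope.

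**Conclusion.** The point holds for the 30-day primary safety outcome. Whichever way enrolled is read, outcomes from discharge to day 30 are not planned for undelivered attempts, and no later analysis can recover them. The direction favours the device unless failed attempts are no riskier than successful ones.

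The size cannot be known from the documents. Under the assumptions above it is about 0 to 2 points for failure shares of 1–5% and event risks of 5–40%, and up to 4.9 points in the worst case. The effect on device and procedural success is conditional on a denominator that the article does not give. This should be fixed because it touches a primary outcome and the remedy is cheap, but it does not undermine the registry as a whole.

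**What to change.** **For attempts still to come**

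- Define the primary safety set as every consented patient in whom the device is introduced into the vasculature, and state plainly whether undelivered attempts are enrolled and in the ITT set.
- Reconcile the two sentences in Screening and Enrollment so that device- and procedure-related events are both recorded for undelivered attempts.
- Obtain their 30-day status by one phone contact. Follow-up already provides for phone contact when a patient cannot be seen in person.
- Use all attempts as the denominator for device and procedural success.
- Keep a separate set for TLPP, labelled as implanted patients.

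Table 2, note a, allows consent after the procedure, up to discharge. A set of consented patients closes the gap only if consent is sought regardless of how the procedure ended, and the wording should say so.

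**For patients already exited**

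Report failed attempts separately, and label the 30-day safety result as limited to delivered patients.

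**Cost**

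Wording in the enrolment and analysis-set sections, a few phone contacts (about 5 to 26 under the assumed failure shares) and slightly less favourable figures.

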#### Intervention

All procedures will be conducted in accordance with each center’s standard of care and patient needs. There are no prohibited concomitant treatments. Deployment of WRAPSODY will be carried out in accordance with the Instructions for Use.

#### Data Monitoring

Safety events will be classified according to the International Organization for Standardization (ISO 14155:2020) definitions. An independent physician adjudicator will review and adjudicate safety events.

### Follow-up

Patients will be followed for up to 24 months. During the 24 month study period, data will be collected at the following timepoints post-procedure: 30 days, 6 months, 12 months, and 24 months. Data collected will include, as available, the following: physical assessment of vascular access circuit, dialysis status, any subsequent intervention(s) on the hemodialysis access circuit, device/procedure-related adverse events (up to 6 months only), and serious device or procedure-related adverse events, including death (Table 2). Patients unable to be assessed in-person at any of the designated timepoints for data collection will be contacted by phone to confirm their status. Upon completion of the study, all patients will be treated according to routine operating practices at the institution of their hemodialysis provider.

**Table 2 Tab2:** Data collection schedule

Assessment	Baseline ≤ 30 Days	Index procedure (Enrollment)	Follow-up assessment 30 days (± 15 days) 6 months (180 ± 30 days) 12 months (360 ± 45 days) 24 months (720 ± 75 days)
Informed consent	X^a^		
Demographics	X		
Medical history	X		
Assessment of fistula or graft/access circuit	X	X	X
Dialysis status	X		X
Index procedure information^b^		X	
Subsequent interventions to access circuit			X
Device and/or procedure related serious adverse events^c^		X	X

^a^ Informed consent will be obtained for all patients prior to index procedure, or as soon as possible after the procedure but no later than time of patient discharge. Informed consent must be collected prior to any study data collection

^b^ The following data will be collected at index procedure through to discharge: lesion pre-treatment (e.g., percutaneous transluminal angioplasty, drug-eluting balloon therapy, thrombectomy); secondary (non-target) lesions (number and treatment) not treated with the WRAPSODY Cell-Impermeable Endoprosthesis; baseline angiographic assessments (e.g., reference vessel diameter, lesion length, predilatation), note: angiographic imaging of procedure will be retained for the duration of the study in case it is required for event adjudication by an independent physician adjudicator; location of stent graft placement; the WRAPSODY Cell-Impermeable Endoprosthesis details (e.g., number, size, and lot numbers); post-treatment of lesion/vessel; assessment of post-stent graft implantation lumen patency via angiogram at the conclusion of the index procedure; evaluation of total procedure time; identification of technical difficulties; adverse event observation, evaluation, and treatment; date of discharge

^c^ All potential device- and/or procedure-related adverse events and all deaths will be collected to 6 months. From 6 months, only serious and device- and/or procedure-related adverse events and all deaths will be collected

Patients may withdraw from the study at any time without prejudice. Reasons for early termination will be documented and data will be evaluated until the time of any patient’s withdrawal. Any patient(s) that withdraws from the study, or is/are lost to follow-up, will not be replaced.

Enrollment in this study began in June 2022; the last patient is expected to be enrolled in 2024 and the last patient visit is expected in 2026.

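### Consent may be given after the procedure, up to discharge, so for patients consented late, entry to the ITT set can depend on the early result

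*Protocol article*

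**What the plan says.** All references are to the protocol article.

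- **Consent timing.** Table 2, footnote a (Follow-up), sets consent "prior to index procedure, or as soon as possible after the procedure but no later than time of patient discharge". It adds: "Informed consent must be collected prior to any study data collection".
- **Consent as a condition of entry.** Table 1 lists as an inclusion criterion: "Patient provides written informed consent for study participation".
- **Enrolment.** Screening and Enrollment says: "All consecutive patients who meet the eligibility criteria will be considered for enrollment in the study". It then says: "All patients who are treated with the WRAPSODY device will be considered enrolled in the study". Of patients in whom delivery of the stent was attempted but not completed, it says: "These patients will be followed through discharge for safety events only and exited from the study".
- **Analysis set.** Under Statistics, the ITT set is everyone enrolled and is primary for all safety and efficacy outcomes. Analyses are descriptive, without hypothesis tests.
- **Outcomes exposed.** Primary safety is the "proportion of patients without any localized or systemic safety events through 30 days post-procedure". It is limited to events that affect the access or venous outflow circuit and lead to reintervention, hospitalization or death; stenosis and thrombosis do not count. Secondary outcomes include the "percentage of patients with device success, procedural success, and anatomic success".

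**The concern.** Read together, these rules let site and patient know how the procedure went, and whether a complication followed, before the patient is asked for or gives consent. A treated patient who dies, is too ill, declines or is not approached before discharge contributes no study data. If such patients had worse early courses than those who consented, the ITT set is selected on an outcome that it is meant to measure.

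The interval before discharge lies inside the 30-day safety window. Device, procedural and anatomic success are probably more exposed still, since their result is likely to be known by the end of the procedure. This is an inference, because the article names these outcomes without defining them. The registry has no comparator and tests no hypothesis, so the absolute proportions are the result and any selection passes straight into them. Enrolling more patients does not reduce it.

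**Working it through.** **Step 1: set the rules side by side.** The enrolment rule counts every treated patient as enrolled. Table 1 and footnote a make consent a condition of entry and of data collection. For a treated patient who never consents, both cannot hold. Taken literally, that patient is either in the ITT set with no data, or outside it although treated. The same applies to a failed delivery: the article provides for recording it, but under footnote a only if the patient consents.

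**Step 2: identify who is affected.** Selection on the early result can act only on patients consented after the procedure, and only through what is known by discharge. Patients consented beforehand, and events after discharge but within 30 days, are not affected by this route.

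**Step 3: illustrate the size.** The plan states no figure to reproduce: 500 was set by clinical consensus, with no expected rates. All four inputs below are assumptions.

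- e: true 30-day event rate
- f: share of patients with events whose event falls before discharge
- L: share of patients consented late, taken as equal with and without events
- w: chance that a late-consent patient with a pre-discharge event is never entered (all other patients are taken as entered)

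Lost fraction: d = e × f × L × w. Observed event rate: (e − d) / (1 − d). Missing patients per 500 entered: 500 × d / (1 − d).

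With e = 5%:

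| f | L | w | d | Observed rate | Bias (points) | Missing per 500 entered |
|---|---|---|---|---|---|---|
| 0.25 | 0.25 | 0.25 | 0.00078 | 4.93% | 0.07 | 0.4 |
| 0.5 | 0.5 | 0.5 | 0.00625 | 4.40% | 0.60 | 3.1 |
| 0.5 | 1 | 0.5 | 0.0125 | 3.80% | 1.20 | 6.3 |
| 0.75 | 1 | 1 | 0.0375 | 1.30% | 3.70 | 19.5 |

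Second row in full: d = 0.05 × 0.5 × 0.5 × 0.5 = 0.00625, and (0.05 − 0.00625) / (1 − 0.00625) = 0.04375 / 0.99375 = 4.40%.

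For the same four settings, the bias runs from 0.03 to 1.49 points at e = 2%, and from 0.14 to 7.30 points at e = 10%.

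**Step 4: compare with the precision reported.** The 95% half-width is 1.96 × √(p(1 − p)/500). For event-free proportions of 98%, 95% and 90% it is 1.2, 1.9 and 2.6 points. Of the four settings, only the extreme one exceeds the half-width, and it does so at all three event rates.

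**The case against.** The strongest reply is that late consent may be rare. Footnote a names consent before the procedure first and otherwise asks for it as soon as possible, and the article does not say how many patients are consented afterwards. This stands: under mild assumptions the bias is negligible. A reader might infer that the safety and success results are certainly biased, or that the whole analysis set is conditioned on a good early course. The documents support neither. They show a route for selection in one group of patients, not that it operated.

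The safety outcome is also narrow, which limits the events that could be lost. A patient who needs reintervention or stays in hospital can still be consented before discharge. Both points stand.

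The article says that consecutive eligible patients are considered. That governs who is approached and does not promise that all are included, so late consent does not falsify it. Nor does it prevent selection at the consent step.

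A reader might also infer that unconsented patients leave no trace. That cannot be shown from a condensed article: screening logs and consent-date fields may be in the full protocol, and their absence here is no fault. A log would, however, measure the selection without removing it.

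Finally, strict prior consent could under-represent urgent cases, against the registry's aim of capturing the full range of patients, and a change during enrolment would mix two consent regimes. This stands, and is why prior consent is proposed as a default with exceptions.

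**Conclusion.** The point holds as a risk that follows from a stated rule. For patients consented after the procedure, entry to the ITT set can depend on the procedural result and on complications before discharge, and the enrolment rule conflicts with the consent rule. The likely direction favours the device for primary safety and for the three success measures; this assumes that patients with a poor early course are less likely to be entered than others consented late.

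The size cannot be derived from the documents. At an assumed 5% event rate it runs from about 0.07 points, through 0.6, to 3.7 points at an extreme that requires every patient to be consented late and every pre-discharge case to be missed. The half-width for comparison is about 1.9 points. The bias may be trivial or may exceed the reported precision, and this article does not allow the reader to tell which.

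**What to change.** 1. For remaining enrolment, make consent before the index procedure the default, with later consent only as a documented exception.
2. Classify every patient by consent date against procedure date. Pre-specify a sensitivity analysis that reports primary safety and device, procedural and anatomic success for the pre-procedure-consent subset beside the full ITT set.
3. As far as ethics approval allows, report the number of patients in whom device placement was attempted but who were not consented.
4. Reconcile the statement that all treated patients are enrolled with the consent criterion and footnote a, so that the ITT denominator is unambiguous.

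If enrolment has closed, items 2 and 4 still apply, and item 3 applies where the counts can be recovered.

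**Cost.** A short amendment and a little more analysis; the target of 500 is unchanged. The subset is smaller, so its intervals are wider. Restricting late consent may lose some urgent cases, and the registry would then hold patients from two consent regimes, which the classification in item 2 makes visible.
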